## Introduction

Psoriasis is a chronic immune-mediated inflammatory disease of the skin and joints.^1 2^ It is recognised by the World Health Organisation (WHO) as a serious non-communicable disease and an area of unmet health need.^3^ Although the exact causes for the onset of psoriasis are not fully understood, they originate in a complex interaction between genetic and environmental factors.^4^ Psoriasis can affect the face, hands, nails, genitals and flexures, therefore, it is both the extent and the location of disease that are important to patients. It is known that the physical, psychological, quality of life, financial and comorbid burden of psoriasis are significant.^5–11^

Psoriasis can affect people of all ages. However, making the diagnosis in children and young people can be more challenging compared with diagnosing psoriasis in adults. Psoriasis is often under-recognised in this younger age group and may be misdiagnosed as other common red scaly rashes such as eczema, viral exanthems and fungal infections. The clinical features seen in childhood disease are often more subtle with thinner plaques, facial involvement and flexural disease in hidden sites normally covered by clothing.^12–14^ Therefore, the diagnosis of psoriasis in children and young people may be missed by non-dermatologists.

Epidemiological data are limited, but it is estimated that one-third of adults with psoriasis first develop skin changes in childhood.^15 16^ Therefore, early and accurate diagnosis presents an opportunity for early intervention. National Institute for Health and Care Excellence (NICE) recommends all children with suspected psoriasis are referred to a dermatology specialist for assessment and management.^17^ This specialist review also includes initiating monitoring for comorbid diseases and assessment for juvenile psoriatic arthritis. Accurate recognition of psoriasis is also important to help paediatric rheumatologists differentiate juvenile idiopathic arthritis into juvenile psoriatic arthritis. This differentiation alters the treatment pathway and likely prognosis for children with juvenile psoriatic arthritis.^18^ Ensuring children and young people receive psoriasis specific treatment and monitoring from the onset is important to help minimise the negative long-term consequences of psoriasis, known as cumulative life course impairment.^19^

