### Secondary objectives

To compare the diagnostic performance of the consensus agreed diagnostic criteria and the best predictive criteria for plaque psoriasis in children and young people.To assess the interobserver variability in the diagnostic criteria assessment.To assess the variability in the reference standard for psoriasis.

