### Participant selection

#### Inclusion criteria

Cases and controls are children and young people aged 0 to <18 years, with active skin disease (rash present) at the time of assessment and are able to consent or have a parent/guardian willing to give consent.

Cases have a confirmed diagnosis of plaque psoriasis by a dermatologist. Plaque psoriasis has been used as a broad term to include all subtypes and presentations of psoriasis where plaques are the main feature. For example, chronic plaque psoriasis, guttate psoriasis, scalp psoriasis and flexural psoriasis are included but purely nail psoriasis or juvenile psoriatic arthritis without skin involvement are excluded. The decision to include guttate psoriasis under the broad description of plaque psoriasis was agreed with the International Psoriasis Council.

Controls have a confirmed diagnosis of a scaly inflammatory rash (excluding psoriasis or indeterminate psoriasis) by a dermatologist. Skin conditions that may be included in the control population are eczema (atopic dermatitis), pityriasis rubra pilaris, pityriasis rosea, ichthyosis, mycosis fungoides, Gianotti-Crosti and tinea corporis. These conditions are not an exhaustive list and the decision as to whether a participant’s skin disease meets the eligibility criteria is made by the patient’s dermatologist.

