### Reference test

A dermatologist’s diagnosis as recorded in the participant’s medical record. The diagnosis is a clinical diagnosis and may include, but does not require, a skin biopsy.

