### Consistency checks

To assess the interobserver variability in the diagnostic criteria assessment, the assessment will be conducted consecutively by two independent assessors in the first forty participants where two assessors are available.

To assess the variability in the reference standard for psoriasis, when optional consent is given, anonymised clinical photographs of cases taken as part of routine clinical care will be sent as anonymised case studies to the twelve consultant dermatologist principal investigators. The consultant dermatologists will be asked to score whether they agree or disagree with the diagnosis of psoriasis.

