### Minimising bias

We have minimised selection bias by asking sites to approach all eligible cases and consecutive controls. All those approached but not recruited will be included in a screening log to demonstrate a non-selective approach. By minimising exclusion criteria, we aimed to design an inclusive study to support generalisation of the results.

The diagnostic criteria assessment will be undertaken by an investigator who is unaware of (blinded to) the dermatologist’s diagnosis of the participant. Investigators are trained to focus on the presence or absence of each clinical feature. The study will test a prespecified scoring algorithm proposed through the eDelphi consensus study and a prespecified diagnostic threshold decided with the expert advisory group.

Bias in the reference standard will be minimised by ensuring all participants have a confirmed diagnosis by a dermatologist. As this is a case–control study, the reference standard will predate the index test. Variability in the reference standard will be examined using clinical photographs.

We have designed the study to include same day recruitment directly from clinic, therefore, the time between the reference standard and index test for most participants will be short. All participants receive the same reference standard (a dermatologist’s diagnosis), therefore, complete verification will be achieved. All participants will be included within the analysis and a complete data set sensitivity analysis is planned. Data are extracted from the medical record by an investigator who did not undertake the diagnostic criteria assessment (blinded to the index test).

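### The reference-standard check names the diagnosis to the raters, so it captures endorsement of the recorded label more than independent diagnosis

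*Protocol article*

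**What the plan says.** The third item under Secondary objectives is "To assess the variability in the reference standard for psoriasis". The Reference test section defines that standard as a dermatologist's diagnosis taken from the medical record: "The diagnosis is a clinical diagnosis and may include, but does not require, a skin biopsy".

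Consistency checks describes how variability will be assessed. For those who agree to it, "anonymised clinical photographs of cases taken as part of routine clinical care will be sent as anonymised case studies". The raters who receive this material are "the twelve consultant dermatologist principal investigators". The task set for them is this: "The consultant dermatologists will be asked to score whether they agree or disagree with the diagnosis of psoriasis". Only cases are shown, and under Inclusion criteria, "Cases have a confirmed diagnosis of plaque psoriasis by a dermatologist".

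Sample size and data analysis summarises the answers by kappa. Minimising bias refers back to the exercise: "Variability in the reference standard will be examined using clinical photographs".

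**The concern.** The variability of a diagnosis is the extent to which dermatologists differ when each makes one. To observe it, each rater has to commit to a diagnosis without being told the recorded one. Here the question contains the recorded answer, and the rater only accepts or rejects it. A consultant who might have written eczema or indeterminate if asked openly can still find psoriasis acceptable once it is named.

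If that happens, observed agreement is higher than unprompted agreement, and the standard looks more reproducible than the exercise can show. This objective is secondary, but every accuracy estimate in the study is read against this standard, so readers will use the result to judge how firm it is. The rating question also decides what data exist: no later choice of statistic can recover independent diagnoses that were never requested.

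**Working it through.** The plan gives no figure for this check, so there is none to reproduce. The argument rests on comparing sections; the arithmetic only illustrates scale.

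**Sections side by side**

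- *Quantity wanted* (Secondary objectives, Reference test): variation in a dermatologist's own clinical diagnosis.
- *Quantity collected* (Consistency checks): agreement or disagreement with a named diagnosis, on sets that all carry that diagnosis.
- *Practice elsewhere in the same article*: the index-test assessor is blinded to the diagnosis (Study flow, Minimising bias), unblinding of that assessor is recorded (Box 2), and the interobserver check uses two independent assessors (Consistency checks). No similar separation is described for the reference-standard check. The raters are also principal investigators, and the published design tells them that every set is a recorded case.

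**Illustration of anchoring (all inputs assumed)**

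Let p be the share of ratings that would be psoriasis if unprompted, and f the share of would-be dissents that naming the label turns into agreement. Observed agreement with the label is

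p + (1 − p) × f.

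| p | f = 0.25 | f = 0.50 |
|---|---|---|
| 0.70 | 0.70 + 0.30 × 0.25 = 0.775 | 0.70 + 0.30 × 0.50 = 0.85 |
| 0.80 | 0.80 + 0.20 × 0.25 = 0.85 | 0.80 + 0.20 × 0.50 = 0.90 |
| 0.90 | 0.90 + 0.10 × 0.25 = 0.925 | 0.90 + 0.10 × 0.50 = 0.95 |

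At p = 0.80, disagreement with the label falls from 20% to between 15% and 10%.

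Agreement between two raters moves the same way. If raters answer independently with the same agree rate a on every set, pairwise agreement is a² + (1 − a)²:

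- unprompted, a = 0.80: 0.64 + 0.04 = 0.68
- a = 0.85: 0.7225 + 0.0225 = 0.745
- a = 0.90: 0.81 + 0.01 = 0.82

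An observed pairwise agreement of 0.82 could therefore come from raters who agree with the label 90% of the time unprompted, or from raters at 80% with half their dissents converted. The planned data cannot tell these apart. The illustration is in raw agreement; it does not give the effect on kappa, the planned statistic.

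**The case against.** The strongest reply is that the article condenses a fuller protocol into one sentence about the rating task, and that a consultant who rejects a named diagnosis still reveals real variation. Both points have force. Disagreements would carry information, so it would be wrong to say that the exercise measures nothing about diagnostic variability. The condensed text also limits what can be claimed about the form. It does not remove the point about the label, because the sentence itself states that the raters are asked about a named diagnosis.

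Four stronger readings are tempting and are not supported.

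- *The scale is forced.* Only agree and disagree are mentioned, but the form is not shown, and an unsure or not-assessable option is neither stated nor excluded.
- *The photographs are inadequate.* The Introduction speaks of "thinner plaques, facial involvement and flexural disease in hidden sites normally covered by clothing", but to explain why non-dermatologists may miss psoriasis. It says nothing about what routine photographs of diagnosed cases leave out, and case studies may carry history as well.
- *A fixed 5 to 15 points of disagreement are artefact.* That takes half of an assumed 10% to 30% of unjudgeable sets. Against 20% baseline disagreement, random scoring would add 0.10 × (0.5 − 0.2) = 3 points to 0.30 × (0.5 − 0.2) = 9 points, and the documents give no unjudgeable share. Such noise would also act against anchoring, so the net direction of error is unknown.
- *The primary sensitivity would change.* Any mislabelling among cases exists whatever the rating form says, and rewording the form would not alter it. No planned primary analysis described in the article uses this check.

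Minimising bias also assigns control of bias in the reference standard to the requirement for a dermatologist's confirmed diagnosis. The photographs are offered only as an examination of variability.

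**Conclusion.** The concern holds in a limited form. Because the question supplies the recorded diagnosis, and only cases are shown, the check captures endorsement of that label more than independent diagnosis, and it serves the third secondary objective poorly. Anchoring may inflate agreement by an amount that the documents do not allow to be estimated. The figures of 85% to 90% from an unprompted 80% rest wholly on an assumed conversion of 25% to 50% of dissents. The primary accuracy estimates are not affected. The change is worth making because it is cheap and must be made in the rating form, not at analysis.

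**What to change.** Do not state the recorded diagnosis on the case study. Ask each consultant for their own most likely diagnosis: psoriasis, indeterminate, another scaly rash (named), or cannot be judged from the material supplied.

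Removing the label is not enough while every set is a case, since the raters can infer it. Mix in existing routine photographs of consenting non-psoriasis participants. Box 2 lists clinical photographs with optional consent and does not restrict them to cases; that the consent covers this use should be confirmed.

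Analyse psoriasis against not psoriasis among the sets judged, report the unjudgeable share separately, and describe the result as photograph-based agreement.

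The cost is a reworded form, a matching analysis sentence, and a few more sets for each consultant to rate, with no extra patients or visits. Reported agreement will probably be lower, and some sets will drop out as not judgeable.

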### Sample size and data analysis

The sample size is based on the primary objective. First, based on a 95% CI that the positive likelihood ratio (LR) is greater than 2 assuming a ratio of 1:1 cases to controls and an estimated sensitivity of 0.8 and specificity of 0.7 the sample size required is 74 cases and 74 controls.^27^

Second, transparent reporting of multivariable prediction models for individual prognosis or diagnosis (TRIPOD) has stated that there are no clear methods for calculating an adequate sample size. The guidance supports the current rule of thumb for sample size calculations of 10 events per variable.^28^ As there are 16 diagnostic features in the consensus agreed diagnostic criteria, a sample size of 160 cases and 160 controls has been calculated.

Participant characteristics will be analysed using descriptive statistics. The diagnostic accuracy of the consensus agreed criteria will be calculated using sensitivity and specificity; 95% CIs will be presented. Multivariate logistic regression analysis will be used to develop the best predictive criteria using the DIPSOC data. The diagnostic features will be entered into the backward regression model. All minor criteria will be entered into the regression model and LR will be presented. Variation of diagnostic accuracy in different clinical contexts will be explored in stratified analysis for the following variables; age at the time of assessment, sex, assessor type and consultation type (new or follow-up).

The results of the multivariate analysis will be plotted on a receiver operator characteristic (ROC) curve and a coefficient threshold determined. The minimum threshold for the best predictive criteria has been set at 0.8 sensitivity and 0.8 specificity after consultation with the expert advisory group (detailed in the acknowledgements). The best predictive diagnostic criteria will be applied to the study data and sensitivity and specificity calculated. The performance of the consensus agreed criteria and the best predictive model criteria will be compared using area under the ROC curve.

Interobserver variability and variability in the reference standard will be calculated using the kappa statistic. Further details on the analysis will be made public in the statistical analysis plan which will be shared on the DIPSOC website www.nottingham.ac.uk/go/dipsoc before the end of recruitment.

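### The stated 74 cases and 74 controls does not follow from sensitivity 0.8 and specificity 0.7; the usual log-scale method needs 120 per group, and 74 leaves the expected lower limit for LR+ at 1.85

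*Protocol article*

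**What the plan says.** The section Sample size and data analysis in the protocol article gives two calculations and ties both to the primary objective.

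The first concerns the accuracy of the consensus criteria. It is "based on a 95% CI that the positive likelihood ratio (LR) is greater than 2", "assuming a ratio of 1:1 cases to controls". The accuracy assumptions and the result are stated together: "estimated sensitivity of 0.8 and specificity of 0.7 the sample size required is 74 cases and 74 controls". The text mentions no power, one-sided limit or particular interval formula; it cites a source for the method.

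The second applies ten events per variable to the 16 consensus features, and from this "a sample size of 160 cases and 160 controls has been calculated". The second figure is the recruitment target: the strengths and limitations list gives 320 participants in total.

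**The concern.** The first calculation states every input it needs, so it can be checked directly, and its result looks too small. An expected LR+ of 2.667 is not far above 2, and with a specificity of 0.7 the false-positive proportion contributes most of the variance. An interval that excludes 2 therefore needs a fairly large sample.

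The first half of the primary objective is to test the accuracy of the consensus criteria. This sentence is the article's only precision calculation for that half, since the events-per-variable rule concerns the regression model. A reader who compares 74 with 160 would conclude that the accuracy question has more than twice the participants it needs. If the true requirement at these inputs is 120, the margin is much thinner.

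**Working it through.** **Inputs** (all from Sample size and data analysis): sensitivity Se = 0.8; specificity Sp = 0.7; lower bound for LR+ = 2; equal groups of size n; 95% interval, read as two-sided, so z = 1.96.

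**Attempt to reproduce 74.** For the usual log-scale interval for a ratio of two independent proportions:

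- LR+ = Se/(1 − Sp) = 0.8/0.3 = 2.667
- Var(ln LR+) = [(1 − Se)/Se + Sp/(1 − Sp)]/n = (0.25 + 2.333)/n = 2.583/n
- ln(2.667/2) = 0.2877
- n = z² × 2.583 / 0.2877² = 2.583 × (1.96/0.2877)² = 119.9, so **120 per group**, not 74. The ratio 120/74 = 1.62.

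**Expected interval at each size**, 2.667 × exp(±1.96 × √(2.583/n)):

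| n per group | Expected 95% CI for LR+ |
|---|---|
| 74 (stated) | 1.85 to 3.85 |
| 120 | 2.00 to 3.56 |
| 160 (planned) | 2.08 to 3.42 |

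**Does another method give 74 from the same inputs?**

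| Method | Two-sided 95% | One-sided 95% |
|---|---|---|
| Log LR+ | 120 | 85 |
| Wald on Se − 2(1 − Sp) | 97 | 68 |
| Score (constrained maximum likelihood) | 108 | 77 |
| Profile likelihood | 105 | 74 |
| Delta method on untransformed LR+ | 159 | 112 |

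Interchanging Se and Sp, or requiring a negative likelihood ratio below 0.5, gives 55. Adding 80% power to the two-sided log method gives 245. The only match is a one-sided profile-likelihood bound (73.5, rounded up), and the article describes neither a one-sided limit nor that method.

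**Which changed input would give 74?** With the two-sided log formula and Sp = 0.73: LR+ = 0.8/0.27 = 2.963; variance term = 0.25 + 0.73/0.27 = 2.954; ln(2.963/2) = 0.3930; n = 1.96² × 2.954/0.3930² ≈ 73.45, rounded up to 74. This is not the only solution. Sensitivity of about 0.86 with Sp = 0.7, or a lower bound of about 1.85 in place of 2, also leads to about 74.

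**Chance that the lower limit actually exceeds 2.** The formula sets only the expected lower limit at 2, with no power term. By normal approximation the probability is Φ(0.2877/√(2.583/n) − 1.96):

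| n per group | Normal approximation | Simulation (400,000 draws, Se 0.8, Sp 0.7) |
|---|---|---|
| 74 | 0.337 | 0.301 |
| 120 | 0.500 | 0.508 |
| 160 | 0.619 | 0.643 |

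**The case against.** The strongest reply is that 74 is not operative. The study size comes from the second calculation; 160 per group exceeds 120, and the expected lower limit there is 2.08. No recruitment number or analysis changes. This stands, and it limits the consequence to the stated justification.

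Second, 120 depends on the method. The article names no formula and cites a source that is not available here; the two-sided methods range from 97 to 159, and the one-sided results straddle 74. This stands as a caution against treating 120 as the only possible answer. It does not rescue the sentence, because the text specifies a 95% confidence interval and every two-sided method applied to LR+ with the printed inputs gives well over 74.

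Third, specificity 0.73 is back-fitted and other changes to the inputs would serve as well. This also stands. The value is a lead to check against the source calculation and should not be inserted without that check.

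Fourth, LR+ above 2 is not a declared success criterion. The consensus criteria are to be reported as sensitivity and specificity with 95% intervals, and the only performance threshold, 0.8 for each, applies to the best predictive criteria. The probabilities above therefore describe what the sample size criterion can deliver; no decision in the plan turns on them. They remain worth stating, since LR+ above 2 is the property chosen to justify the sample size.

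**Conclusion.** The concern holds. The sentence gives a complete set of inputs and a result that those inputs do not produce. By the standard two-sided log-scale method the requirement is 120 per group (97 to 159 across the two-sided methods tried), and at 74 per group the expected 95% interval of 1.85 to 3.85 fails the stated criterion. This rests on reading the 95% interval as two-sided and on the criterion being an expected lower limit of 2 with no added power, which is all that the article states.

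The error is in the justification. The planned 160 + 160 meets the criterion in expectation (2.08 to 3.42), but with less room than the 74 implies: even if both assumptions are exactly right, the chance of a lower limit above 2 is about 62–64%. A rounded or mis-transcribed specificity is a plausible cause but cannot be confirmed from the article.

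**What to change.** Check the source calculation and correct the sentence so that it reproduces:

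- If sensitivity 0.8 and specificity 0.7 are the intended assumptions, replace 74 with 120 cases and 120 controls, and name the interval method.
- If the source calculation shows that a different input was used, such as specificity 0.73, keep 74 and print that input to the precision the calculation needs. Between specificity 0.70 and 0.73 the requirement moves from 120 to 74, so one decimal place is not enough.

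Then add what the planned size delivers: with 160 per group at 0.8 and 0.7, an expected 95% interval for LR+ of 2.08 to 3.42 and about a 62% probability (64% by simulation) that the lower limit exceeds 2.

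The cost is one corrected sentence and one added sentence. The recruitment target need not change.

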Box 1Sixteen diagnostic features agreed by the International Psoriasis Council to be important for the diagnosis of plaque psoriasis in children (26). Two additional diagnostic features (*) have also been included that were close to reaching consensus and were emphasised as important in the feedback from experts.Major criteriaScaly erythematous plaques on the extensor surfaces of the elbows and knees.Scaly erythematous plaques on the trunk triggered by a sore throat or other infection.Raindrop plaques typical of guttate disease on the trunk or limbs.Minor criteriaScale and erythema in the scalp involving the hairline.Retroauricular erythema (including behind the earlobes).Scaly erythema inside the external auditory meatus.Persistent well-demarcated erythematous scaly rash anywhere on the body.Fine scaly patches involving the upper thighs and buttocks.Well-demarcated erythematous rash in the napkin area involving the crural folds.Persistent erythema in the umbilicus.Nail pitting.Onycholysis of the nail(s).Subungual hyperkeratosis of the nail(s).Positive family history of psoriasis.Koebner phenomenon.Fusiform swelling of a toe or a finger suggestive of dactylitis.*Persistent well-demarcated facial rash with fine or absent scale.*Natal cleft erythema and/or skin splitting.

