### Index test

A diagnostic criteria assessment looking for the presence or absence of each of the diagnostic features (box 1). Using the same assessment, the index test is divided into index test 1 and index test 2.

#### Index test 1

The international eDelphi consensus study agreed 16 diagnostic features of childhood psoriasis and separated them into major and minor criteria. In the consensus study, a scoring algorithm was proposed where the presence of one or more major criteria or three of more minor criteria would support a diagnosis of psoriasis. Together these 16 diagnostic features and the scoring algorithm form index test 1.^26^

#### Index test 2

Two additional features were close to reaching consensus and were emphasised as important in the feedback from the expert participants. These 18 items will be used to create the best predictive criteria using multivariate analysis. The best predictive criteria form index test 2.

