**Figure 1 F1:**
[figure not shown]
Developing DIagnostic criteria for PSOriasis in children study flow. CRN, Clinical Research Network.

After informed consent has been taken, all participants undergo the same research visit. The visit comprises demographic questions, quality of life questionnaires (for those aged 4–17 years) and a diagnostic criteria assessment by a study investigator who is blinded to the participant’s diagnosis (blinded to the reference standard). The two quality of life questionnaires are the Children’s Dermatology Life Quality Index and the Child Health Utility 9D.

Each participant is offered a certificate, sticker and voucher to say thank you for taking part. Following the research visit, information is extracted from the medical record by an investigator who did not perform the assessment (blinded to the index test). Data to be extracted include the reference standard (diagnosis of skin disease), duration of disease, disease severity and current treatments. A summary of the data variables collected in the DIPSOC study is presented in box 2.

Box 2A summary of the data variables collected in the DIPSOC studyResearch visitDemographic information: age, sex, ethnicity, household occupation.Diagnostic criteria assessment: presence and absence of each of the 18 diagnostic features (index test).Clinical experience of the diagnostic criteria assessor.Unblinding of the diagnostic criteria assessor.Quality of life questionnaires (4–17 years)—CDLQI and CHU-9D.Contact details (optional consent).Medical recordParticipant’s diagnosis (reference standard).Age at diagnosis.Age at onset of symptoms.Skin biopsy result.Disease severity.Presence of psoriatic arthritis.Current skin treatments—topical, systemic, phototherapy.Clinical photographs (optional consent).CDLQI, Children’s Dermatology Life Quality Index; CHU-9D, Child Health Utility 9D; DIPSOC, Developing DIagnostic criteria for PSOriasis in Children.

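### The 10-events-per-variable sample size counts 16 features, but the regression it supports starts from 18 candidates; on that reading 160 cases give 8.9 events per candidate variable

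*Protocol article*

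**What the plan says.** Under Sample size and data analysis, the Protocol article gives two calculations. The first concerns the positive likelihood ratio and asks for 74 cases and 74 controls. The second concerns the prediction model and sets the final size. It adopts a rule ("The guidance supports the current rule of thumb for sample size calculations of 10 events per variable") and applies it: "As there are 16 diagnostic features in the consensus agreed diagnostic criteria, a sample size of 160 cases and 160 controls has been calculated".

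The Index test section separates two tests built on the same assessment. Index test 1 is the 16 consensus features plus a scoring algorithm proposed in the consensus study (at least one major or at least three minor criteria). Index test 2 is the best predictive criteria: "These 18 items will be used to create the best predictive criteria using multivariate analysis".

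Box 1 explains the difference in count: "Two additional diagnostic features (*) have also been included that were close to reaching consensus and were emphasised as important in the feedback from experts". Box 2, under Study flow, lists among the data collected the "presence and absence of each of the 18 diagnostic features (index test").

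On the model itself, the Sample size and data analysis section says "The diagnostic features will be entered into the backward regression model", followed at once by "All minor criteria will be entered into the regression model and LR will be presented".

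**The concern.** An events-per-variable rule limits how many coefficients are estimated from a given number of events. It has meaning only for a fitted model, and under backward selection the relevant count is the candidates entered, not the variables that survive. Here the count of 16 comes from the test that is not fitted, while the fitted test is said to start from 18 items. Nothing in the article explains why the two added items were left out of the count.

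This calculation determines the size of the study, since the likelihood-ratio calculation asks for less than half as many participants. A reader is told that the model has 10 events per variable. If the candidate set is the one described under Index test 2, it has fewer. The figure matters for how the results are read: the model is selected, its threshold is chosen on the ROC curve, and its sensitivity and specificity are calculated on the same study data.

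**Working it through.** **Inputs**

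- Events per variable required: 10 (Sample size and data analysis).
- Count used in the calculation: 16 (same section).
- Planned cases and controls: 160 and 160, total 320 (same section; the total also stands in the Strengths and limitations summary).
- Candidates for index test 2: 18 (Index test). Box 1 confirms it by counting: 3 major + 13 minor = 16 consensus features, plus 2 starred = 18.

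**Step 1: reproduce the stated figure.** Cases = events per variable × number of variables = 10 × 16 = 160. With 1:1 controls that is 160 + 160 = 320, which matches exactly. The multiplication is right; the question is whether 16 is the right input.

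**Step 2: the limiting group.** With equal groups, the smaller outcome group is 160 whichever group is called the event, so 160 is the correct numerator.

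**Step 3: repeat with the candidate set of index test 2.**

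- Events per candidate variable = 160 / 18 = 8.89.
- Shortfall against 10 = (10 − 8.89) / 10 = 11%.
- Cases needed by the stated rule = 10 × 18 = 180, so 180 + 180 = 360 in total. That is 20 more per group, or 20/160 = 12.5%.

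**Step 4: other readings of the candidate set.** The sentence on minor criteria could mean that only minor criteria enter the model.

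| Candidate set | Candidates | 160 / candidates | Rule of 10 met? |
|---|---|---|---|
| All items in Box 1 | 18 | 8.9 | No |
| Minor plus the two starred items | 15 | 10.7 | Yes |
| Minor only, without the starred items | 13 | 12.3 | Yes |
| Count used in the calculation | 16 | 10.0 | Yes |

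The last row would require fitting the 3 major and 13 minor criteria and dropping the two starred items. That contradicts the Index test section, which puts both into the model.

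**The case against.** The strongest reply is that the candidate set is not settled. If the sentence on minor criteria is restrictive, there are 15 or 13 candidates and the rule is met with room to spare. This stands as a possibility, so the 8.9 is conditional. It is still the weaker reading: the sentence just before it refers to the diagnostic features without restriction, and the Index test section gives 18 outright. Nor does it rescue the calculation as printed, because it does not produce 16.

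A second reply is that 10 is only a rule of thumb. The article says so itself and reports that the guidance it cites recognises no clear method for sizing such a model. This also stands. Moving from 10 to 8.9 breaches no power requirement, and nothing in the article allows the resulting overfitting to be quantified.

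A third reply is that details are left to the statistical analysis plan. That does not answer this point, which is not an omission: the article prints a derivation that conflicts with its own description of the model.

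The same reply does bar a stronger inference. A reader might conclude that overfitting goes uncorrected because no shrinkage is planned. The article does not mention shrinkage, but it defers further analysis details to a plan that is not at hand, so that conclusion cannot be drawn. Prescribing a uniform shrinkage factor would not be the natural remedy either. Multiplying every coefficient by one positive constant leaves the ranking of participants unchanged, and with it the ROC curve, its area and every attainable pair of sensitivity and specificity, which are the results the article names.

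**Conclusion.** The sample-size paragraph uses the wrong count for the model it is meant to support. On the best-supported reading, with 18 candidates, 160 cases give 8.9 events per candidate variable and not 10; the stated rule would give 180 cases and 180 controls. This rests on two assumptions: that all 18 items in Box 1 enter the backward regression, and that each present/absent feature counts as one variable. If only minor criteria enter, the rule is met at 10.7 or 12.3, but the printed justification by 16 features is still not the one that applies.

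The defect is an inconsistent input, not a multiplication error, and its size is modest. A reader might infer that the study is too small to develop the criteria, but missing a rule of thumb by 11% does not show that. A reader might also infer that the effective figure is lower still for signs that are rarely present. The article gives no feature prevalences, so the documents offer no basis for such a figure.

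**What to change.** State the candidate set for the backward regression once, so that the Index test section and the Sample size and data analysis section agree, and make clear whether the sentence on minor criteria restricts the model or not.

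If the set is the 18 items, replace the justification by 16 features with wording such as: *160 cases give 8.9 events per candidate variable for the 18 candidate features; the rule-of-thumb figure of 10 is not met.* If the set is smaller, give its count and the matching figure (10.7 for 15 candidates, 12.3 for 13).

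Recruitment stays as planned. The change costs a sentence or two and can be carried by the statistical analysis plan, which the article says will be shared before recruitment ends. The only downside is a slightly less favourable stated figure if the set is 18.
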